## Methods/Design

### Design

PCMR evaluation includes analysis of its implementation and of its effects. We posit that the program concept and implementation will adjust to the different CSSS settings. The proposed evaluation will use a mixed design that involves two complementary research strategies [35]. The first strategy is a quasi-experimental "before-after" design, based on a quantitative approach; it will look at the program's effects and their variations among the six settings where it is implemented. This situation corresponds to a natural experiment in which researchers have no control on the intervention being introduced.

The second strategy is consistent with a multiple case study approach, where each of the six settings constitutes a case. This strategy is based on qualitative methods and will characterize the variable represented by the implementation context. A monograph for each setting will be produced following analysis and will include data on the various indicators described below. The monographs will explain the processes that have led to the effects observed and the particular contextual conditions that can be linked to differences in implementation and effects. Adding this component to the evaluation will therefore increase both internal and external validity.

The two strategies will generate data that we will triangulate to provide a deeper explanation of the link between degree of program implementation, context and observed effects. Triangulation will be based on an interpretative analysis of the data collected and on a validation process with individuals responsible for implementing the PCMR through discussion groups that will also serve as mediums for knowledge translation and exchange.

### Indicators, data sources and analyses

#### Objective 1

To meet this objective, the indicators measuring the effects of the PCMR (Additional file 1) will be compared at different stages of the program as well as among various implementation settings. For each patient, follow-up at the cardiometabolic risk education centre determined in the PCMR will extend over 24 months.

Several of the **indicators for patients **pertain to control of patients' biological parameters (HbA1c, BP, lipid profile, body mass index, waist circumference) and lifestyle habits (diet, physical activity, smoking). These indicators include measures of change during the intervention as well as measures of attainment of clinical targets at the end of the evaluation (e.g. proportion of patients with HbA1c ≤ 7%). Data needed to calculate indicators of biological parameters and lifestyle habits for each patient will be taken from the regional computerized registry for chronic illnesses. These data will be compiled in the registry at program entry and then at the 3^rd^, 6^th^, 12^th^, 18^th ^and 24^th ^month of follow-up.

Indicators for health services utilization by patients in the PCMR, their experience of care, follow-up of diabetes and/or hypertension, self-management and quality of life will be measured using a 20-minute self-administered questionnaire, in French or English, given to patients by the nurse or nutritionist at the cardiometabolic education centre upon program entry, and at 12 and 24 months of follow-up (Additional file 2 and Additional file 3). The questionnaire will be completed on site, with support provided for patients with low literacy levels when required. A postal questionnaire will also be administered 36 months after onset of follow-up (Additional file 3). Data collected at 36 months--a year after the end of follow-up in the program--will be used to check the persistence of effects post-intervention. The first section of the questionnaire focuses on patients' utilization of health services (medical visits, hospitalizations, visits to emergency) during the previous year. The second section documents patient affiliation to the primary care physician who provides diabetes and/or hypertension follow-up and who referred him or her to the education centre, the characteristics of affiliation (duration, frequency and place of consultation), as well as certain attributes related to the patient's care experience with this physician (accessibility, continuity, comprehensiveness and perceived care outcomes). Questions in this section are adapted from the population survey questionnaire developed for a study carried out by our research team aimed at assessing the evolution of primary healthcare organizations and their performance (2005-2010) in two regions of Québec province [36]. Section 3 of the questionnaire concerns management and follow-up of chronic illnesses. These questions are adapted from the *Patient Assessment of Chronic Illness Care *questionnaire [11]. The 4^th ^section is on patient self-management and quality of life related to their diabetes and/or hypertension. Self-management is measured using questions adapted from the *Summary of Diabetes Self-Care Activities*, and assesses the frequency of self-management behaviours during a typical week (preventive behaviours--diet, physical activity, smoking abstinence--as well as compliance with medication as prescribed, glycemia and BP monitoring) [37]. Questions measuring patients' quality of life are adapted from the questionnaire *Audit of Diabetes Dependent Quality of Life *[38-40]. Data on patients' sociodemographic characteristics and health status are the subject of the last section of the questionnaire. Linking patient data to data collected from his or her physician will allow us to determine how primary care services are organized at the place where the patient is seen. A questionnaire will also be administered to patients who withdraw from the PCMR prematurely; it will include questions designed to document the reasons why a person drops out (Additional file 4).

Use of health services by patients in the PCMR will also be documented with medical administrative data (medical services, hospitalizations, emergency room visits), using the patient's health insurance number to match medical administrative data to data from the regional computerized registry on chronic illnesses and to his or her survey data.

Regression models will be built to assess the program's effects on patients, in terms of biological parameters, lifestyle habits, health services utilization, chronic illness follow-up, self-management, quality of life and care experience, based on the CSSS, degree of exposure to the program, patient characteristics, and organizational characteristics of primary care clinics where patients are seen. Particular attention will be paid to patients' sociodemographic characteristics (male/female, age, income, education) in terms of equity of access to services. Linear models will be constructed for continuous dependent variables (e.g. before-after intervention differences in HbA1c or BP). Logistic models will be used for dichotomous dependent variables (e.g. clinical targets achieved or not by the end of the intervention, dichotomized indices). Longitudinal analyses will enable us to model the evolution of dependent variables throughout the follow-up period. These analyses will be performed using multilevel models (Generalized Linear Mixed Models) [41] in which individual repeated observations will be nested within patients. We will thus be able to control for certain fixed subject characteristics as well as for time-varying covariates.

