#### Patient recruitment and power calculation

We plan on recruiting about 250 patients a year in each participating CSSS, for a total of 3500 patients over 28 months. Assuming that recruitment rate is constant, we estimate that the 2000 patients recruited in the first 16 months could be the object, during the study, of at least three observations for data collected using questionnaires, and at least six observations for clinical data (Table 1). For the 1500 patients recruited during the last 12 months of recruitment, we will have two observations for data collected using questionnaires and at least four observations for clinical data. We expect that an initial sample of 3500 subjects, with an attrition rate of 20%, would ensure 2800 subjects available for analyses over two time measures. This sample size would allow detection of a difference in average between two territories that is about 0.14 in standard deviation units in longitudinal linear models, and about 7%, with a power of 80% at the 0.05 significance level in logistic models [42,43]. These calculations are conservatively based on the number of subjects measured twice; use of effective covariables or of a higher number of observations per subject should lead to an increase in the power of models.

**Table 1 T1:** Patient recruitment and numbers of data collected

Number of patients	Questionnaires (services utilization, affiliation to primary care physician, chronic illness monitoring, self-management, quality of life)	**Registry ****data ****(biological measures and lifestyle habits)**
500 patients recruited in first 4 months	0, 12, 24 and 36 months	0, 3, 6, 12, 18 and 24 months

500 patients recruited in months 5 to 8	0, 12 and 24 months	0, 3, 6, 12, 18 and 24 months

500 patients recruited in months 9 to 12	0, 12 and 24 months	0, 3, 6, 12, 18 and 24 months

500 patients recruited in months 13 to 16	0, 12 and 24 months	0, 3, 6, 12, 18 and 24 months

500 patients recruited in months 17 to 20	0 and 12 months	0, 3, 6, 12 and 18 months

500 patients recruited in months 21 to 24	0 and 12 months	0, 3, 6 and 12 months

500 patients recruited in months 25 to 28	0 and 12 months	0, 3, 6 and 12 months

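### Before-after change and end-of-intervention target attainment are given to models that need an end value, although the mixed models already planned could estimate both from all recruits

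*Protocol article*

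**What the plan says.** The regression paragraph under Objective 1 (Indicators, data sources and analyses) assigns outcomes to three kinds of model.

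- Continuous outcomes: "Linear models will be constructed for continuous dependent variables (e.g. before-after intervention differences in HbA1c or BP".
- Binary outcomes: "Logistic models will be used for dichotomous dependent variables (e.g. clinical targets achieved or not by the end of the intervention, dichotomized indices".
- Repeated outcomes: "Longitudinal analyses will enable us to model the evolution of dependent variables throughout the follow-up period". These are to be "multilevel models (Generalized Linear Mixed Models) [41] in which individual repeated observations will be nested within patients".

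The indicator description at the start of the Objective 1 text places target attainment at the end of the evaluation, whereas the logistic sentence places it at the end of the intervention. Programme follow-up is 24 months per patient, with registry values at entry and at months 3, 6, 12, 18 and 24.

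On numbers, Patient recruitment and power calculation says "We plan on recruiting about 250 patients a year in each participating CSSS, for a total of 3500 patients over 28 months" and that this sample, "with an attrition rate of 20%, would ensure 2800 subjects available for analyses over two time measures". On leavers, the Objective 1 text says "A questionnaire will also be administered to patients who withdraw from the PCMR prematurely", to document their reasons. It describes no use of that information in the outcome models.

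Objective 1 concerns the patients enrolled in the programme, by site and degree of exposure. Strengths and limitations acknowledges that there is no control group.

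**The concern.** A difference from entry cannot be computed without a later value, and whether a target was met at the end cannot be scored without an end value or a rule for its absence. Choosing these as dependent variables therefore restricts the sample to patients still being measured, which is narrower than the population named in Objective 1.

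Two features make this matter more here. First, a single-group before-after design has no comparison arm in which selective loss could cancel. Second, leaving the programme probably also ends measurement: the 12- and 24-month questionnaires are completed at the education centre, and the registry is that centre's clinical tool.

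If leavers fare differently from stayers, the estimated effect shifts. If attrition also differs between CSSS, the territory comparison shifts too. Early leavers have low exposure to the programme, so leaving them out also narrows the range of one of the explanatory variables.

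**Working it through.** **Inputs from the protocol article.** 250 patients a year per CSSS; 6 CSSS; 28 months of recruitment; 20% attrition; the measurement schedule in Table 1.

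**1. The plan's own figures.**
- Recruits: 250 × 6 × 28/12 = 3500, as stated.
- After attrition: 3500 × (1 − 0.20) = 2800, as stated.

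**2. Who can have a month-24 registry value (Table 1).**
- Recruitment months 1 to 16: 4 × 500 = 2000 patients have month 24 scheduled. 2000/3500 = 57%.
- Recruitment months 17 to 28: 3 × 500 = 1500 patients do not. The last scheduled registry value is month 18 for 500 of them and month 12 for 1000.
- Applying the stated 20% to the 2000 (an assumption, since the article gives one overall rate): 2000 × 0.80 = 1600. 1600/3500 = 46%.
- Without a month-24 value: 3500 − 1600 = 1900, made up of 1500 from late recruitment and 400 from attrition.

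The 2800 exceeds the 2000 with month 24 scheduled, so it cannot be a count of month-24 completers. It counts patients with two measures at any times. The article thus leaves open which value is the after value.

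**3. Possible bias in mean change.** Let D be the mean change in stayers and f × D the mean change in leavers, with 20% leavers. The full-cohort change is (0.8 + 0.2f) × D, and the overstatement is 1/(0.8 + 0.2f) − 1. The values of f are assumed.

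| f | Full-cohort change | Overstatement |
|---|---|---|
| 1 (same as stayers) | 1.00 D | 0% |
| 0.5 | 0.90 D | 11% |
| 0 (no change) | 0.80 D | 25% |

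**4. Possible bias in target attainment.** Assume 60% of stayers reach target and that 20% leave. The full-cohort proportion is 0.8 × 60% + 0.2 × p, where p is attainment in leavers.
- p = 60%: 60%, no overstatement.
- p = 50%: 58%, 2 points.
- p = 40%: 56%, 4 points.
- p = 30%: 54%, 6 points.

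**5. Territory comparison (all inputs assumed).** Take 60% in stayers and 30% in leavers in both territories, with attrition of 10% in one and 30% in the other.
- 0.9 × 60% + 0.1 × 30% = 57%.
- 0.7 × 60% + 0.3 × 30% = 51%.

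A 6-point gap over all recruits would appear as 60% against 60%, that is, zero. With equal attrition and equal leaver outcomes, both territories shift by the same amount and no false difference arises.

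**The case against.** The strongest reply is that the article writes no completer rule. It names model families with examples, gives no analysis set, and may leave missing-data handling to an analysis plan that is not shown. It also plans mixed models, and the Objective 3 text assigns repeatedly measured outcomes to multilevel longitudinal models; HbA1c and BP are such outcomes. The continuous detectable difference is quoted for longitudinal linear models. A patient who leaves after month 6 has registry values at 0, 3 and 6 months, so a before-after difference could be computed if the after value were not fixed at month 24. Linked administrative data on service use do not depend on attendance.

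Much of this stands, and it rules out several stronger readings that a reader might infer:

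- **That the main effect is completer-only.** No analysis is named as primary or headline, and the planned mixed models can keep early leavers' observations.
- **That the effect is likely overstated.** This needs leavers to do worse than stayers. No passage says so, and the overstatement is zero if they do equally well.
- **That 46% measures those who stayed.** Most of the shortfall, 1500 of 1900, is administrative and is not linked in the documents to poor progress.
- **That a 6-point bias nearly equals the detectable 7%.** The 7% is a difference between two territories, whereas the 6 points are a shift in one pooled proportion.

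The reply does not remove the fact that the article itself names before-after differences and end-of-intervention targets as outcomes of the linear and logistic models. That is a stated choice of dependent variable, and it sits beside a stated alternative that does not need an end value.

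**Conclusion.** The point holds as a choice between methods the article already contains. As described, the change-score and end-target models can use only patients with an end value. If the end is month 24, that value is scheduled for 57% of recruits and expected for about 46%, the latter assuming that the 20% attrition applies at month 24. These estimates may be biased for the enrolled population, and for comparisons between territories whose attrition differs.

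The size cannot be determined from the documents. With 20% leavers, mean change is overstated by 0% to 25% as the leavers' assumed change falls from equal to stayers' to none. This treats the late-recruitment losses as unrelated to outcome. The territory example shows only what could happen, since nothing in the article indicates unequal attrition.

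The mixed models are the better source for both estimates. They use each recruit's available values and are valid when dropout depends on observed data, a weaker condition than the end-value models need. They do not protect against dropout that depends on unobserved outcomes, so a sensitivity analysis is still needed. The two descriptions of the end also have to be reconciled.

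**What to change.** 1. State that end-of-intervention change and the proportion at target are estimated from the mixed models already planned, fitted to all recruits with an entry value. The entry value should be among the modelled observations, so that a patient with no later value is still included. For binary targets, average the fitted probabilities over the full entry cohort.
2. Define one end time point and use it in both the indicator description and the regression paragraph. Say how recruits from months 17 to 28, who have no scheduled month-24 value, contribute to it.
3. Keep the change-score and end-point logistic models as secondary analyses, and state the number of patients in each.
4. Report attrition by CSSS beside every territory estimate, separating late recruitment from withdrawal.
5. Add a sensitivity analysis for outcome-related dropout that varies the assumed outcome in leavers. No change from entry can be one scenario; it is debatable as an imputation and should not serve as the main analysis.

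The cost is revised analysis wording and some extra model work. No new data are needed. The reported effect may become slightly less favourable.

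### Dichotomised indices are named as outcomes for logistic models; any graded index analysed only in that form would lose about 36% to 51% of its information in a between-territory comparison

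*Protocol article*

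**What the plan says.** In the protocol article, section Indicators, data sources and analyses, Objective 1, the model follows the type of outcome. For continuous outcomes: "Linear models will be constructed for continuous dependent variables (e.g. before-after intervention differences in HbA1c or BP". For binary outcomes, logistic models are planned, with these examples: "clinical targets achieved or not by the end of the intervention, dichotomized indices". Repeated measures go into generalized linear mixed models: "Longitudinal analyses will enable us to model the evolution of dependent variables throughout the follow-up period".

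The outcome domains listed there include chronic illness follow-up, self-management, quality of life and care experience, all measured by questionnaire. At least one is graded by nature: the self-management section "assesses the frequency of self-management behaviours during a typical week".

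The section Patient recruitment and power calculation gives separate detectable differences for the two kinds of model, "about 0.14 in standard deviation units in longitudinal linear models, and about 7%, with a power of 80" percent. They rest on 2,800 analysable patients: "with an attrition rate of 20%, would ensure 2800 subjects available for analyses over two time measures".

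**The concern.** An index that has to be dichotomised has more than two values to begin with. Cutting it treats patients just either side of the cut as different, and patients far apart on the same side as equal. For HbA1c or blood pressure targets the cut has a clinical meaning, and HbA1c and blood pressure changes are also modelled as continuous. The indices are listed separately from those targets, and the text gives no such reason for cutting them.

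At stake is power for small effects. Objective 1 looks for differences among six territories, and the questionnaire outcomes have the fewest observations: by Table 1, 1,500 of the 3,500 patients have only two. The same approach carries over to the physician outcomes, and Objective 3 again uses logistic models for dichotomous outcomes.

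**Working it through.** **Inputs from the protocol.** 3,500 recruited, 20% attrition, 2,800 analysable, six territories (2,800/6 = 467 each); detectable differences of about 0.14 SD (linear) and about 7 points (logistic); power 80%, significance level 0.05.

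**Assumptions not in the documents.** Two-sided test; normal index; share of patients beyond the cut between 50% and 20%.

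**1. The plan's own figures.** With z = 1.960 + 0.842 = 2.802, one territory against the other five (467 v 2,333) gives 2.802 × √(1/467 + 1/2,333) = 0.142 SD. For proportions, 46.5% v 53.5% has 79.0% power. Both stated figures are therefore reproduced. Two single territories (467 v 467), with no credit for repeated measures, give 0.183 SD and about 9.1 points. How the plan labels that contrast is a separate matter. The relative loss below does not depend on it.

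**2. Information kept after a cut.** For a between-group comparison of a normal score with a share p beyond the cut c, the information kept is E = φ(c)² / [p(1 − p)], where φ is the normal density. Power after the cut, for an effect with 80% power on the score, is Φ(2.802 × √E − 1.960). The detectable effect becomes 0.14/√E.

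| Cut | Information kept | Lost | Power (80% on the score) | Detectable effect |
|---|---|---|---|---|
| 50:50 | 0.399²/0.25 = 0.637 | 36% | 61% | 0.175 SD |
| 30:70 | 0.348²/0.21 = 0.576 | 42% | 57% | 0.185 SD |
| 20:80 | 0.280²/0.16 = 0.490 | 51% | 50% | 0.20 SD |

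**3. Simulation.** With 467 v 2,333 patients, a shift of 0.14 SD and 4,000 runs, power was 80% on the score, 61% after a median split and 53% after a 20:80 cut. The formula in step 2 is a small-effect approximation, which is why the last figure differs a little from 50%.

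**4. Consistency with the plan's two detectable effects.** Near 50%, 7 points on a normal score is 0.07/0.399 = 0.175 SD, and (0.14/0.175)² = 0.64, in line with the first row. Conversely, a 0.14 SD shift moves a median-split proportion by 0.399 × 0.14 = 5.6 points, less than the 7 points stated as detectable. Both stated figures are rounded: 0.135 to 0.145 SD against 6.5 to 7.5 points gives a ratio anywhere from about 0.52 to 0.79.

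**5. Before-after contrasts.** Here the information kept is E(1 − ρ)/(1 − r), with ρ the before-after correlation of the score and r that of its binary version. At a median cut and ρ of 0.3, 0.5 or 0.7 (assumed), r is 0.194, 0.333 or 0.494, and the loss is 45%, 52% or 62%. The documents give no ρ, so this only shows direction.

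**The case against.** The strongest reply is that the words are a bracketed example. A reader might infer that all questionnaire indices are to be dichotomised, and that a third to a half of the information on those outcomes will certainly be lost. The documents do not support that. They name no index, do not say that every index is cut, and do not exclude linear or mixed models of the same scores. HbA1c and blood pressure appear both as change and as target attainment, and the indices could be handled in the same double way. An index may also be nearly binary: the self-management section covers smoking abstinence and taking medication as prescribed. This stands, and it makes the point conditional.

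Second, the definitions and cut-points may sit in the additional files or an analysis plan. This also stands: their absence from the article is no finding. The choice to dichotomise, however, is stated in the article.

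Third, a reader might take the 0.14 SD and 7 points as the plan's own proof of a 36% loss. They are not. They are general, rounded figures for two kinds of model, and the ratio appears only once a normal score and a cut near 50% are assumed. They agree with the textbook loss but do not establish it.

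Fourth, dichotomies have a use, since percentages are easier for managers to read. This stands as a reason to report them, but not to make them the only analysis.

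**Conclusion.** The point holds in conditional form. The article names dichotomised indices as outcomes for logistic models, apart from clinical targets and without a stated reason. For any graded index analysed only that way, a between-territory comparison loses about 36% of the information at a 50:50 cut and about 51% at 20:80. Power falls from 80% to about 61% or 50%. This assumes a roughly normal score and a cut in that range. The loss is less if the index is nearly binary, and can be more for before-after contrasts or more extreme cuts. If the undivided scores are modelled as well, most of the concern disappears. It does not extend to the clinical targets.

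**What to change.** In the regression paragraph of Objective 1, state that for any graded index the undivided score is the main outcome (transformed, or treated as ordinal, if skewed), using the linear or generalized linear mixed models already planned. Keep logistic models for outcomes that are binary by nature and for clinical targets set in advance. Report any dichotomised index as secondary or descriptive, with its cut fixed before the data are seen. Carry the same rule to the physician outcomes and Objective 3.

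The cost is a change of analysis wording, with no new data or patients. A mean score difference is slightly less intuitive for managers than a percentage, and the secondary report covers that need.

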**Indicators concerning the impact on medical practice **will be measured for participating general practitioners using a 15-minute self-administered mail-in questionnaire, in French or in English, the first time one of his or her patients attends the cardiometabolic risk education centre, and then at 12, 24 and 36 months (Additional file 5 and Additional file 6). In addition to questions pertaining to physicians' sociodemographic and professional characteristics, the questionnaire also documents the organizational characteristics of their clinics using questions from the 2010 survey of primary care clinics used in our previous project [36]. One section of the questionnaire deals with physicians' practices regarding management of patients with diabetes or hypertension; these questions are adapted from the questionnaire by Nutting et al. [44]. The questionnaire for physicians administered at 12, 24 and 36 months includes several questions on their assessment of the PCMR: participation in the program, impacts on their patients and on their practice, relationships with specialized services, strengths and weaknesses of the program, as well as barriers and facilitating factors. The data analysis strategy will be similar to the one used to assess the effects of the program on patients. Physician and clinic characteristics will be utilized as covariables to construct regression models that measure the program's effects on their management of chronic diseases and their perceptions of the effects on patients and on their own practice.

#### Objective 2

Two elements are required to meet the goals. The first consists in assessing the level of PCMR implementation in various CSSS based on four criteria: 1) completeness of the components with regard to the program initially planned by the ASSSM; to assess the degree of implementation, we will measure the differences between the program planned by the ASSSM and the one actually implemented in CSSS; 2) intensity of the effort made to conduct program activities (e.g. number of training sessions, number of patients); 3) integration of the PCMR into CSSS program activities; and 4) program penetration rate among the targeted populations. This will be estimated by calculating the proportion of patients with diabetes or hypertension followed in the PCMR among patients with diabetes or hypertension in each participating CSSS territory (estimated using the medical services and hospitalizations administrative data).

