Two approaches will be used to attain this objective. The first is designed to complement the analysis proposed in Objective 2. Using the material compiled in the monographs, quantitative variables and categorical taxonomic variables will be created and integrated into regression analyses explaining the effects of the program. Regression models will be built to assess the influence of the variables pertaining to PCMR set up and implementation in the various CSSS on the effects observed among patients, controlling for degree of exposure to PCMR, patient characteristics and the characteristics of primary care clinics where they are seen. Given the low number of upper level units (6 CSSS), variables linked to CSSS will be considered as fixed effects in regression models. Linear regressions will be constructed for continuous dependent variables, while logistic models will be used for dichotomous dependent variables and multilevel longitudinal models for dependent variables that are the object of repeated measures. A similar analysis strategy will be used to assess the influence on medical practice of variables that reflect PCMR set up and implementation in various CSSS.

The second approach will be interpretive: from the material used to produce the monographs, participants' statements on the relationship between program effects and components will be noted and analyzed. Conclusions drawn from these two approaches will be validated in discussion groups.

#### Objective 4

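### As described, the patient models carry no physician or clinic level, so tests of clinic characteristics and territory contrasts are too liberal if outcomes correlate within clinic

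*Protocol article*

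**What the plan says.** - **Objective 1, longitudinal models for patients.** These are "multilevel models (Generalized Linear Mixed Models) [41] in which individual repeated observations will be nested within patients". No level above the patient is named.
- **Objective 1, single-time models.** Linear models for before-after differences and logistic models for attained targets are described without any cluster term. The explanatory variables for all patient models include "organizational characteristics of primary care clinics where patients are seen".
- **Objective 1, patient questionnaire.** The physician following the patient's diabetes or hypertension is also the one "who referred him or her to the education centre". The article adds: "Linking patient data to data collected from his or her physician will allow us to determine how primary care services are organized" in the patient's usual setting. Several questionnaire items rate care received from that physician.
- **Objective 1, medical practice.** The strategy is said to resemble the one for patients: "Physician and clinic characteristics will be utilized as covariables to construct regression models".
- **Objective 3.** "Given the low number of upper level units (6 CSSS), variables linked to CSSS will be considered as fixed effects in regression models". These models also control for "patient characteristics and the characteristics of primary care clinics where they are seen".
- **Patient recruitment and power calculation.** With 2800 analysed subjects, 80% power and a 0.05 level, the detectable difference between two territories is put at about 0.14 SD or about 7%. The calculation is called conservative because it counts subjects measured twice. It mentions neither an ICC nor a design effect.

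**The concern.** Patients of one physician or clinic share prescribing habits, follow-up routines and organisation, and several outcomes are ratings of that physician. Such patients are unlikely to be independent given territory. A covariate that is constant within a clinic gains information mainly from the number of clinics, whereas a model without a clinic level credits it with the number of patients. Territory contrasts share the problem because each territory mean is an average over its clinics.

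The reason given for fixed effects, the small number of units, is offered for the six CSSS. It says nothing about the level between patient and CSSS.

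At stake are the comparisons the study presents as its main contribution: differences between territories (Objective 1) and the influence of context and organisation on effects (Objective 3). If the standard errors are too small, organisational factors and territory differences will be declared associated with effects too often, and the authors intend to extrapolate those findings to other settings.

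**Working it through.** **1. Reproduce the stated figure.** Inputs from the power section: 250 patients a year in each of 6 CSSS over 28 months, with 20% attrition.

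- Recruited: 250 × 6 × 28/12 = 3500. Analysed: 3500 × 0.8 = 2800, or 2800/6 = 466.7 per territory.
- Detectable difference in SD units = (1.960 + 0.842) × √(1/n₁ + 1/n₂), two-sided 5% assumed.
- One territory against the other five: 2.802 × √(1/466.7 + 1/2333.3) = 0.142 SD. For proportions near 50%, multiply by 0.5: 7.1 points.
- Two single territories, one measure each: 2.802 × √(2/466.7) = 0.183 SD. This falls to 0.14 only with an unstated within-patient correlation of about 0.71 (change scores) or 0.65 (baseline-adjusted).

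Both routes to 0.14 treat patients as independent, so the figure contains no allowance for clustering.

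**2. Add clustering.** With m patients per physician or clinic (equal sizes) and an ICC for the quantity analysed:

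- Design effect DE = 1 + (m − 1) × ICC
- True SE / naive SE = √DE
- Type I error of the naive test = 2 × [1 − Φ(1.96/√DE)]
- Detectable difference = stated value × √DE

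Both m and ICC are assumptions, since the article gives neither.

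| m | ICC | DE | SE ratio | Type I error | 0.14 SD becomes | 7% becomes |
|---|---|---|---|---|---|---|
| 5 | 0.01 | 1.04 | 1.02 | 5.5% | 0.143 | 7.1% |
| 5 | 0.05 | 1.20 | 1.10 | 7.4% | 0.153 | 7.7% |
| 5 | 0.10 | 1.40 | 1.18 | 9.8% | 0.166 | 8.3% |
| 10 | 0.01 | 1.09 | 1.04 | 6.0% | 0.146 | 7.3% |
| 10 | 0.05 | 1.45 | 1.20 | 10.4% | 0.169 | 8.4% |
| 10 | 0.10 | 1.90 | 1.38 | 15.5% | 0.193 | 9.6% |
| 20 | 0.01 | 1.19 | 1.09 | 7.2% | 0.153 | 7.6% |
| 20 | 0.05 | 1.95 | 1.40 | 16.0% | 0.195 | 9.8% |
| 20 | 0.10 | 2.90 | 1.70 | 25.0% | 0.238 | 11.9% |

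If the test is made valid and the sample stays the same, power for 0.14 SD falls from 80% to 78% in the first row and 38% in the last.

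**3. Do fixed CSSS effects remove the problem?** A simulation used six territories with 47 clinics of 10 patients or 23 clinics of 20 in each, one continuous value per patient, fixed territory effects, one clinic covariate and no clinic effect in the fitted model (2000 replicates per setting). Rejection rates at nominal 5%:

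| Patients per clinic | ICC | Territory contrast | Clinic covariate |
|---|---|---|---|
| 10 | 0.01 | 6.1% | 6.0% |
| 10 | 0.05 | 11.3% | 9.9% |
| 10 | 0.10 | 15.5% | 14.6% |
| 20 | 0.01 | 6.6% | 6.8% |
| 20 | 0.05 | 16.6% | 14.0% |
| 20 | 0.10 | 26.0% | 25.2% |

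With ICC = 0, every rate lay between 4.85% and 5.6%. Fixed CSSS effects absorb variation between territories but not variation between clinics inside a territory, so both kinds of test are affected.

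**4. Level or change?** Write a patient's value at time t as clinic intercept + clinic slope × t + patient terms. In a within-patient change the clinic intercept cancels and the clinic slope remains. For before-after differences and time interactions, the ICC that matters is therefore that of change. A clinic random intercept alone would leave those standard errors uncorrected.

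**The case against.** The strongest reply is that the article names one nesting to explain how repeated measures are handled and never says it is the sole level. A condensed article may leave further random effects, or a robust variance, to a fuller plan. This stands in part: the text does not exclude a clinic effect, and the case is weakest for the physician models, where no nesting is stated at all. But the article does set out the hierarchy, and when it discusses upper-level units it means the six CSSS. Someone following it as written would fit no clinic level.

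Second, the size is unknown. The harm needs a positive correlation that remains after CSSS effects and clinic covariates, and the number of clinics and physicians is still to be learned from the start-up interviews. Education and individual follow-up come from the CSSS education centre, so the physician or clinic correlation may be small for lifestyle, self-management and weight. This stands fully and is why the range starts at 5.5%.

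A reader might also go further than the article allows, in three ways:

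- That the standard errors are certainly too small, or that 25% is the expected error rate. Neither follows without an ICC.
- That the overall before-after findings are undermined. Within-patient trends and patient-level coefficients are much less affected.
- That the inflation should start from 0.183 SD. The article states 0.14 SD for longitudinal models. How that figure fits a two-territory contrast is a separate question.

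**Conclusion.** The point holds in conditional form. The stated structure omits the grouping by physician and clinic while using clinic-level predictors, and fixed CSSS effects do not make up for it. Whenever the within-cluster correlation of the analysed quantity is positive, tests of clinic characteristics and territory contrasts reject too often.

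The excess may be trivial (5.5% at 5 patients per cluster and ICC 0.01) or serious (25% at 20 and 0.10). The article cannot settle which. It is probably largest for care-experience and chronic-illness follow-up ratings, and smaller for outcomes driven by the education centre. The range rests on equal cluster sizes, a two-sided 5% test and the assumed m and ICC. The power statement has the same gap, so describing it as conservative is not justified as it stands.

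**What to change.** - **Longitudinal patient models:** add a clinic-level random intercept (and a physician one where numbers allow) plus a clinic-level random slope for time, or use clinic-clustered robust variance.
- **Single-time linear and logistic models:** use a clinic random intercept or clinic-clustered robust standard errors.
- **Physician models:** account for clinic in the same way.
- **CSSS:** keep as fixed effects.
- **Power section:** restate 0.14 SD and 7% with an assumed cluster size, ICC and design effect, and drop the description as conservative unless this is done.

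The cost is somewhat wider intervals and slightly more complex models. The patient-physician link is already planned and the physician questionnaire already covers the clinic, so no new data are needed.
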